In addition to the responder/non-responder phenomenon, and the question of whether low-response to one form of exercise training necessarily implies low-response to all modalities, a question relates to genetic predisposition to adaptation. Classical twin studies utilising monozygotic (MZ) and dizygotic (DZ) twin pairs have long been used to assess the contribution of unmeasured genetic and environmental effects on variation in measured traits [10,11]. Since MZ twins theoretically share 100%, and DZ twins ~50%, of their DNA [12] then a phenotype that is purely explained by genetics would hold a ratio of 2:1 consisting of correlations of 1 for MZ and 0.5 for DZ [13]. If the 2:1 ratio remains the same but the correlations are lower than these values, then both shared and unshared components may be influencing results [14,15]. In this way, classical twin studies allow researchers to stratify the total variance of a phenotype. Any excess correlation observed for MZ compared with DZ pairs is assumed to be due to the extra genetic material shared by MZ twins (under the equal environments assumption [16]), and the amount and proportion of variation in a measured trait due to additive genetic effects (A), shared environmental effects (C) and unshared effects (E) can be determined. The proportion of the total variation which is due to A is often referred to as the heritability [12,17]. Alternately, in cases where genetic and environmental effects cannot be separated, the use of a classical twin study design may make it possible to estimate the extent of familial aggregation [18].

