### Participant recruitment

2.3

Healthy, same-sex DZ and MZ twin pairs, between the ages of 16–40yrs, were recruited to participate in the study. Recruitment started in September 2016 and was facilitated by Twins Research Australia (formerly Australian Twin Registry [33]). Twin pairs in the Metropolitan Perth-based region were sent emails, newsletters and conventional mail regarding participation in the study. Other recruitment methods included advertising in local and Perth-based newspapers, online and social media recruiting, The University of Western Australia (UWA) email lists, flyers around UWA and nearby establishments, and word of mouth. Baseline demographic data is displayed in Table 1, and a participant flow chart in Fig. 1.

**Table 1 tbl1:** Baseline characteristics of participants enrolled in the study.

		Monozygotic (MZ)	Dizygotic (DZ)
		n = 62 (31 twin pairs, 18 F, 13 M)	n = 28 (14 twin pairs, 10 F, 4 M)
		Mean (SD)	Mean (SD)
Age (yrs)	F	24.2 (5.0)	23.8 (4.2)
	M	28.0 (5.9)	22.9 (5.3)
	Total	26.2 (6.1)	23.5 (4.5)
Height (cm)	F	170.2 (4.0)	168.6 (5.9)
	M	180.8 (4.5)	178.0 (6.6)
	Total	174.5 (6.5)	171.8 (7.5)
Weight (kg)	F	67.0 (19.6)	59.3 (9.4)
	M	81.0 (12.8)	69.1 (11.3)
	Total	74.9 (18.9)	62.6 (10.9)
BMI (kg/m^2^)	F	23.0 (6.1)	20.9 (2.8)
	M	24.7 (3.6)	21.7 (2.7)
	Total	24.4 (5.3)	21.1 (2.9)

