### Exercise training protocols

2.6

Exercise interventions were centre-based and supervised by a qualified sport scientist or an accredited exercise physiologist (AEP). Sessions were either in the morning or late afternoon/evening to avoid the heat of the day and to accommodate participant work schedules. Participants attended three exercise sessions a week at UWA. A standardised warm up and cool down were conducted in each session. If an injury prevented an individual from completing their prescribed exercise, then that individual and their twin were to complete a modified exercise instead. This ensured that twin pairs were receiving equivalent physiological stimulation throughout the study. Adherence to the training program was required to be 80% or higher across both interventions in order for the twin pair to be included in final analyses.

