The primary objective of the current study is to estimate the MZ and DZ correlations and the variance components A, C and E for each outcome measure cross-sectionally, and in response to exercise training (END and RES). In STATA mixed models effects will calculate intraclass correlation coefficients (r) for MZ and DZ twin pairs. Covariates to be adjusted for (e.g. sex, fat-free mass, VO_2max_, baseline data) will depend on the primary outcome measure. The subsequent rMZ and rDZ, and their respective P-values and 95% confidence intervals will be presented. Differences between intraclass correlations (rMZ vs rDZ) will be assessed using the likelihood-ratio test in STATA to compare mixed effects models constraining covariances for MZ and DZ pairs to be equal with models allowing different covariances for MZ and DZ pairs [69]. If the model allowing different MZ and DZ covariances are significantly better, and rMZ are significantly different to rDZ, A, C and E will then be calculated from the estimates of the DZ covariance and the additional MZ covariance, and confidence intervals for A, C and E will be estimated using the delta method. When rMZ and rDZ are not significantly different then a single model that includes all twin pairs but constrains the covariance to be equal for MZ and DZ pairs will be used in STATA to calculate C and E components only, and their respective 95% confidence intervals. An additional model which estimates covariance for MZ twins but fixes the DZ covariance to be zero will test if the estimated correlations suggest that the equal environments assumption has been violated.

Secondary objectives of this study will be addressed using the individual change with training (END and RES) results for each outcome measure. Response rates for each modality can be derived as a percentage of positive responses (>0) and compared against one another by a Z-test. Concordances can be derived as the percentage of individuals who positively respond to both exercise training modalities (Supplementary Fig. 5). In a similar way to the correlation analyses, within-twin pair concordances for MZ and DZ can be derived for each exercise intervention and compared to each other.

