### Sample size and power

3.2

Power analysis is based on our primary outcome measures which are highly specialized and sensitive; vascular function (FMD), cardiac and cerebrovascular adaptation. Our cardiac publications [6,8,9] have reported significant effects in fewer subjects (n = 10 and n = 13 per group) than we recruited in the present study; we observed highly significant differences utilising highly sensitive MRI. Regarding cerebral measures, previous publications and our pilot work demonstrate that cerebral blood flow is increased in older individuals (n = 9, 65–78 yrs) by 10% after intervention. Our previous twin study publications in a paediatric population [24,31] cross-sectionally revealed FMD correlations of 0.6 and 0.38 in MZ and DZ twin pairs, respectively, in a smaller sample size of 22 (11 pairs) per group [24]. In addition, this study applied an exercise intervention (8 weeks) shorter than the current study (12 weeks), and produced correlations of 0.74 and 0.37 for FMD responses in MZ and DZ groups (n = 24–6 pairs per group) [31]. A power analysis (G*Power v3.1.2), performed using the predicted correlations for rMZ = 0.80 and rDZ = 0.30, assuming alpha = 0.05, indicates that a sample size of 23 individuals in each group provides 80% power.

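### The ACE rule has no step for rMZ > 2 × rDZ, so behind the significance gate its typical result, at the document's own correlations and 31/14 pairs, is a negative C and an A above rMZ

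*Protocol article*

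**What the plan says.** The Introduction describes A, C and E as shares of variance. It says the twin design yields "the amount and proportion of variation in a measured trait due to additive genetic effects (A), shared environmental effects (C"), with E as the unshared remainder, and it equates heritability with A's share of the total. The genetic premise is "Since MZ twins theoretically share 100%, and DZ twins ~50%, of their DNA".

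Planned statistical analysis then sets the procedure for the primary objective. A likelihood-ratio test compares a model with separate MZ and DZ covariances against one with a common covariance. If the correlations differ significantly, "A, C and E will then be calculated from the estimates of the DZ covariance and the additional MZ covariance", with delta-method intervals. If they do not, a model with C and E only is fitted. A further model with the DZ covariance fixed at zero serves as a check on the equal environments assumption.

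Sample size and power gives the "predicted correlations for rMZ = 0.80 and rDZ = 0.30" and an earlier exercise study that "produced correlations of 0.74 and 0.37 for FMD responses in MZ and DZ groups". It also gives cross-sectional FMD correlations of 0.6 and 0.38. Table 1 gives "n = 62 (31 twin pairs, 18 F, 13 M") for MZ and "n = 28 (14 twin pairs, 10 F, 4 M") for DZ. The training analyses may use fewer pairs: "Adherence to the training program was required to be 80% or higher across both interventions".

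**The concern.** The procedure provides for rMZ and rDZ that do not differ, but not for an rMZ more than twice rDZ. In that case the calculation returns a negative shared-environment component and a genetic component larger than the whole MZ resemblance. Neither can be read as a proportion of variance, which is how the Introduction defines them.

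This matters because A, C and E for every outcome, at baseline and for each training mode, are the primary objective. With few DZ pairs, the significance test passes mainly samples in which rDZ happens to be low, and these are the samples in which the formula leaves its range. A reader could then be shown a heritability of training response near or above 100% when the true value is much lower.

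**Working it through.** **The plan's own figure.** For 0.80 against 0.30, Fisher's q = atanh(0.80) − atanh(0.30) = 0.789. One-sided at alpha 0.05 with 80% power, n = 2((1.645 + 0.842)/0.789)² + 3 = 22.9, so 23 per group as stated (two-sided: 28.2, so 29). This confirms which correlations the plan relied on. Power is not the point here.

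**Formula.** Under 100%/50% sharing, covMZ = A + C and covDZ = A/2 + C. The additional MZ covariance is D = covMZ − covDZ = A/2. Hence, on a standardised scale:
- A = 2D = 2(rMZ − rDZ)
- C = covDZ − D = 2rDZ − rMZ
- E = 1 − rMZ

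Since A + C = rMZ, the conditions C < 0, A > rMZ and rMZ > 2 × rDZ are one and the same event. A > 1 requires rMZ − rDZ > 0.50.

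**The document's correlations put in.**

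| rMZ / rDZ | A | C | E |
|---|---|---|---|
| 0.80 / 0.30 (prediction) | 1.00 | −0.20 | 0.20 |
| 0.74 / 0.37 (FMD response) | 0.74 | 0.00 | 0.26 |
| 0.60 / 0.38 (FMD, cross-sectional) | 0.44 | 0.16 | 0.40 |

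**What the gate lets through, approximately.** With 31 and 14 pairs, the Fisher z standard error is √(1/28 + 1/11) = 0.356, and two-sided significance needs a difference of 1.96 × 0.356 = 0.697. The largest rDZ that is significantly below rMZ is then:

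| Observed rMZ | Largest significant rDZ | rMZ/2 | A there | C there |
|---|---|---|---|---|
| 0.60 | 0.00 | 0.30 | 1.21 | −0.61 |
| 0.70 | 0.17 | 0.35 | 1.06 | −0.36 |
| 0.74 | 0.25 | 0.37 | 0.98 | −0.24 |
| 0.80 | 0.38 | 0.40 | 0.84 | −0.04 |
| 0.85 | 0.51 | 0.425 | 0.69 | +0.16 |

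By this approximation, every significant result with observed rMZ up to 0.80 has C < 0. At 0.85 it need not.

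**Simulation with the plan's own type of test.** Bivariate normal pairs, 31 MZ and 14 DZ, common variance, maximum likelihood, 1-df likelihood-ratio test at P < 0.05. Ranges are over repeated runs.

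| True rMZ / rDZ | Reach ACE branch | C < 0 among these | A > 1 among these |
|---|---|---|---|
| 0.74 / 0.37 | 49–53% | 80–84% | 52–57% |
| 0.60 / 0.38 | 19–20% | 90–95% | 60–71% |
| 0.80 / 0.30 | 81% | 79–82% | 60–64% |

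Holding the covariances non-negative, as a random-effects fit does, hardly changes this: 83%/56%, 95%/68% and 82%/64% in the same row order.

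**Separating the formula from the gate.** Over all data sets, mean A is 0.75–0.76 at 0.74/0.37 (true 0.74) and 0.44–0.46 at 0.60/0.38 (true 0.44). Among gated results it is 1.12 and 1.15–1.24. C is still negative in about 48–49% and 36–37% of ungated data sets.

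**Sensitivity.** Larger shared environment (assumed values, not in the document): C < 0 in 28–40% of released results at 0.80/0.60, 22–25% at 0.90/0.60 and 8% at 0.95/0.70. Fewer pairs: the number lost to the adherence rule is not given. With 25 and 11 pairs assumed and a Fisher z gate, C < 0 rises from 90–99% to 94–100%, and A > 1 from 75–91% to 86–98%.

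**The case against.** The strongest reply is that the formula itself is sound. Unbounded estimates are nearly unbiased over all data sets, while bounding them throughout pulls A down (mean 0.55 against a true 0.74, and 0.36 against 0.44). An out-of-range value also signals misfit that a bound would hide. This largely stands. A reader might infer that the formula by itself always overstates heritability, or does so by exactly the size of the negative C. The document does not support that: A − rMZ = −C is an identity in the sample, not an error against the truth, and the one-way inflation comes from reporting A only after a significant test. What remains is that the plan does gate the result, so the unbiasedness does not carry over to what is reported.

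A second reply is that the article prints no formula, cites a source for the model comparison and may leave boundary handling to a fuller plan. The formula is indeed inferred. But the text fixes the gate, the inputs to A, C and E, the interval method and the fallback, and the stated sharing leaves little room for another reading.

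Third, the model with zero DZ covariance does look at low DZ resemblance. It tests an assumption, however, and changes no estimate of A or C.

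Finally, rMZ and rDZ with intervals are to be presented anyway, so an impossible value would be visible. That softens the harm but gives no valid estimate of A.

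**Conclusion.** The point holds in limited form. As written, the ACE branch has no step for rMZ > 2 × rDZ, and the plan's predicted correlations fall there. With 31 and 14 pairs, formula and gate together make an inadmissible result typical at each correlation pair the document gives: C < 0 in about 80–95% and A above 100% in about 53–71% of released results. This assumes normal data, equal variances in MZ and DZ twins, all enrolled pairs retained, and the inferred formulas.

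Two stronger readings should be avoided. One is that most ACE results for every outcome would be inadmissible. The document gives correlations only for FMD and one planning pair, and where shared environment is large the share falls well below half. The other is that a significant difference in the wrong direction would often yield a negative A. It occurs in fewer than 1% of data sets, and it cannot occur if the additional MZ covariance is held non-negative.

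**What to change.** Add to Planned statistical analysis, for the ACE branch only: where the estimated MZ covariance exceeds twice the DZ covariance, C is fixed at 0, the AE model is fitted, and A is reported from that model. Note that rMZ > 2 × rDZ may reflect sampling error or non-additive effects. Show the unconstrained rMZ, rDZ, A and C beside the AE result so that misfit stays visible.

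The cost is a few lines of text and one extra model per affected outcome on the same data. Some headline heritabilities become smaller, and some boundary bias is accepted. In simulation, bounding A and C at 0 brings mean A in the ACE branch from 1.12 to 0.73 at 0.74/0.37 (true 0.74). At 0.60/0.38 it still averages about 0.63–0.65 against a true 0.44. The refit keeps A within the MZ resemblance but does not remove all the inflation from the gate.

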### Objectives

2.1

1.Primary objective: Assess the contribution of genetic and environmental effects on variation in cross-sectional data, and END and RES training responses, for each outcome measure2.Secondary objectives:a.Assess whether individual response to training differs between modalities for each outcome measureb.Assess whether the concordance between response to END and RES modes of training will differ between individuals

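### A is calculated only when rMZ and rDZ differ significantly; otherwise the pooled covariance is reported as C, so a non-significant test with 31 MZ and 14 DZ pairs stands in for proof that A = 0

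*Protocol article*

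**What the plan says.** Section 3 (Planned statistical analysis) states the target: "The primary objective of the current study is to estimate the MZ and DZ correlations and the variance components A, C and E", for baseline data and for the response to each training mode. Section 2.1 (Objectives) has the same scope: "variation in cross-sectional data, and END and RES training responses, for each outcome measure".

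The components are then made conditional on a likelihood-ratio test that compares a model with separate MZ and DZ covariances against one with a common covariance. Section 3 sets P < 0.05 as the default level. The two branches are:

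- **Test significant:** if the separate-covariance model fits significantly better "and rMZ are significantly different to rDZ, A, C and E will then be calculated", and "confidence intervals for A, C and E will be estimated using the delta method".
- **Test not significant:** "When rMZ and rDZ are not significantly different then a single model that includes all twin pairs but constrains the covariance to be equal" across zygosities is used "to calculate C and E components only".

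rMZ and rDZ, with P-values and 95% confidence intervals, are presented in either case.

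The Introduction defines C as shared environment. It also says that "in cases where genetic and environmental effects cannot be separated" a twin design may still estimate familial aggregation. Section 3 does not give that name to the result of the non-significant branch.

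**The concern.** Under the usual twin model the MZ covariance is A + C and the DZ covariance is A/2 + C. A common covariance fitted to both groups is therefore a mixture of A and C. It equals C only if A is zero, and a non-significant test in a small sample does not show that. The non-significant branch thus assigns genetic resemblance to shared environment. The significant branch reports only those A values large enough to pass the test.

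The components are the quantities the study sets out to estimate. Hypothesis 1 (section 2.2) compares heritability between cross-sectional and training data. If A is zero by constraint in one dataset and selected for being large in the other, that comparison partly reflects which dataset passed the test.

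**Working it through.** **Inputs.** Table 1: 31 MZ and 14 DZ pairs. Section 3: 5% level. Section 3.2 (Sample size and power): planning correlations 0.80/0.30, earlier FMD training-response correlations 0.74/0.37, earlier cross-sectional FMD correlations 0.60/0.38. The pair 0.60/0.30 is an added assumption for illustration.

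**Step 1: the plan's own figure.** The Fisher-z sample size for comparing two independent correlations is n = 2[(z_alpha + z_beta)/(atanh rMZ - atanh rDZ)]^2 + 3 per group. Here atanh(0.80) - atanh(0.30) = 1.0986 - 0.3095 = 0.7891.

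- One-sided: 2 x [(1.645 + 0.842)/0.7891]^2 + 3 = 22.9, so 23. This reproduces the stated 23 for 80% power.
- Two-sided: 2 x [(1.960 + 0.842)/0.7891]^2 + 3 = 28.2, so 29.

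In this formula n counts the observations behind each correlation, which are twin pairs.

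**Step 2: components implied by each pair of correlations.** A = 2(rMZ - rDZ), C = 2rDZ - rMZ.

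- 0.74/0.37: A = 0.74, C = 0.
- 0.60/0.38: A = 0.44, C = 0.16.
- 0.60/0.30: A = 0.60, C = 0.
- 0.80/0.30: A = 1.00, C = -0.20.

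**Step 3: what the pooled covariance estimates.** As a first approximation, weight by pairs: [31(A + C) + 14(A/2 + C)]/45 = C + (38/45)A = C + 0.84A. About 84% of A is counted in the component reported as C.

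- 0.74/0.37: 0 + 0.844 x 0.74 = 0.62.
- 0.60/0.38: 0.16 + 0.844 x 0.44 = 0.53.

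**Step 4: simulation of the stated rule.** Bivariate normal pairs, common mean and variance, 31 MZ and 14 DZ pairs, 1-df likelihood-ratio test at chi-square > 3.841, 3000 runs per row.

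| rMZ/rDZ | Implied A, C | Test significant | Significant: mean A, mean C | Not significant: A, mean C | Over both branches: A, C | A with no test |
|---|---|---|---|---|---|---|
| 0.74/0.37 | 0.74, 0 | 54% | 1.09, -0.33 | 0, 0.63 | 0.59, 0.11 | 0.77 |
| 0.60/0.38 | 0.44, 0.16 | 19% | 1.14, -0.47 | 0, 0.52 | 0.22, 0.33 | 0.46 |
| 0.60/0.30 (assumed) | 0.60, 0 | 27% | 1.22, -0.55 | 0, 0.50 | 0.33, 0.22 | 0.60 |
| 0.80/0.30 (planning) | 1.00, -0.20 | 80% | 1.20, -0.39 | 0, 0.68 | 0.95, -0.18 | 1.04 |

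Repeat simulations put the first row's significance rate between about 50% and 55%. The Fisher-z approximation (two-sided) is lower: 35% for the first row and 13% for the second. The simulated C in the non-significant branch agrees with Step 3.

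The average over branches can be checked by hand. At 0.74/0.37, A = 0.538 x 1.09 = 0.59 and C = 0.538 x (-0.33) + 0.462 x 0.63 = 0.11.

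**Step 5: where the inflation comes from.** At 0.60/0.38 the smallest absolute A among significant runs was 0.43, almost the implied value of 0.44. Almost any A that passes the test therefore exceeds the truth. The last column shows that the same estimator without the test is close to unbiased, so the selection causes the bias.

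**Step 6: effect on Hypothesis 1.** Take two datasets that both have A = 0.60 and C = 0. If their tests were independent (an assumption, since the same people supply both), exactly one would pass in 2 x 0.267 x 0.733 = 39% of trials. That would set an A of 0 beside one averaging 1.22, with no true difference.

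**The case against.** Four points can be made for the plan.

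- **The correlations are never withheld.** rMZ and rDZ with intervals are part of the stated objective and are shown for every outcome, so a reader can form 2(rMZ - rDZ). This stands. It means heritability information is not hidden, but the components the study reports are still wrong.
- **The simpler model is a familiar choice when the richer one fits no better.** If A is truly zero this does little harm: at 0.50/0.50 the test is significant in 5.5% of runs and C averages 0.48 in the rest. With 14 DZ pairs, however, the same result is common when A is substantial.
- **The Introduction knows the limit, and section 3 adds a check that fixes the DZ covariance at zero.** The Introduction gives the right reading but section 3 does not apply it. The added model is aimed at the equal environments assumption and does not change what is reported when the test fails.
- **At the planning correlations the rule does little net harm to A.** This stands, but those values imply a negative C, and neither earlier FMD result quoted in section 3.2 matches them.

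A reader might infer more than the documents support:

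- **Overall bias in both directions.** The inflation and the zeroing belong to separate branches. At the correlations examined in the table, net A is too low and net C too high.
- **An explicit conclusion of no genetic contribution.** The plan does not commit to one; it calculates C and E only.
- **Unbounded estimation as the fault, with a fit restricted to 0-1 as the cure.** The untested, unbounded estimate is nearly unbiased. A bounded fit at 31/14 pairs gave mean A of 0.41 for a true 0.60 and 0.56 for a true 0.74.
- **A multiplicity failure.** Adjustment across outcomes and the choice of named primary variables are commonly left to an analysis plan that is not shown here.

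**Conclusion.** The concern holds in this form: the rule lets a non-significant comparison of 31 MZ and 14 DZ pairs set A to zero and reports mixed resemblance as shared environment. At the protocol's own earlier FMD correlations that happens in roughly half of trials (0.74/0.37) and four in five (0.60/0.38). It gives C of about 0.63 and 0.52 where 0 and 0.16 are implied. When the test passes, mean A is about 1.1 against 0.74 and 0.44. At the planning values the net bias in A is small (0.95 against 1.00).

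These sizes assume normal data, equal variances in the two zygosity groups, no covariates, and all enrolled pairs analysed. Section 2.6 restricts final analyses to pairs with at least 80% adherence, so the training datasets may be smaller and the test weaker. The exact sizes depend on the true correlations. The mislabelling of the pooled covariance does not: it arises whenever A is above zero.

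**What to change.** In section 3, remove the condition. For every outcome, at baseline and for each training response, report A, C and E with confidence intervals from the model that lets MZ and DZ covariances differ, whatever the test result. Keep the likelihood-ratio P-value as a descriptive statistic. Continue to present rMZ and rDZ with their intervals, as already planned.

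If the common-covariance model is kept, label its component familial aggregation (A and C not separated), in line with the Introduction, and never C. Base Hypothesis 1 on the unconditional estimates and their intervals.

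The change needs only wording and a little code, and no new data. The price is visibly wide intervals and some estimates outside 0-1, which should be shown as they fall because they reflect what 14 DZ pairs can support.

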#### Zygosity DNA testing

2.7.1

A DNA cheek swab was obtained following written consent during the participants’ first testing session to determine zygosity of twin pairs for inclusion in the study (EasyDNA AU, Springwood, QLD). Four swabs were taken in total, two swabs on each side of the participants mouth, rubbed ten times against the inside of the participants cheek. Participants collected, packaged and sealed their own samples to eliminate the risk of cross-contamination. Samples were sent to an independent genetics laboratory for testing of zygosity as the probability based on genetic markers of twin pairs being either MZ or DZ. Participants elected whether they would receive the results of the DNA test. When initially recruiting for the study twin pairs self-reported their zygosity, however when they were DNA zygosity tested 10 self-reported DZ twin pairs were actually found to be MZ. Therefore, DNA zygosity testing was a major strength within the current study as heritability is determined based on zygosity. Nearly 25% of twin pairs self-reported zygosity was incorrect in our study and our results could have been very different if DNA samples had not been acquired. A systematic review and meta-regression has also concluded that self-reported rather than DNA tested zygosity has a significant effect on heritability results [35].

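### The model with DZ covariance fixed at zero does not test the equal environments assumption, and with 14 DZ pairs its result says almost nothing about it

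*Protocol article*

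**What the plan says.** Section 3 (Planned statistical analysis) estimates rMZ and rDZ for each outcome and compares them by a likelihood-ratio test. A, C and E are derived where the correlations differ significantly, and C and E only where they do not. It then adds a model with a free MZ covariance that "fixes the DZ covariance to be zero will test if the estimated correlations suggest that the equal environments assumption has been violated". It does not name the comparison model, the result that would count as a violation, or what would follow from one.

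The Introduction gives the logic of the design. "Any excess correlation observed for MZ compared with DZ pairs is assumed to be due to the extra genetic material shared by MZ twins", and this holds "under the equal environments assumption". It adds that a purely genetic trait "would hold a ratio of 2:1 consisting of correlations of 1 for MZ and 0.5 for DZ".

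Table 1 lists 31 MZ and 14 DZ pairs. Section 2.6 can only lower these numbers for the training-response analyses: "Adherence to the training program was required to be 80% or higher across both interventions" before a pair enters the final analyses.

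**The concern.** The stated method and the stated purpose do not match. Fixing the DZ covariance at zero asks whether DZ twins resemble each other at all. The equal environments assumption concerns something else: whether MZ twins resemble each other partly because they share more environment than DZ twins do. By the Introduction's own 2:1 rule, the boundary for an additive trait is rDZ = rMZ/2, not rDZ = 0.

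Every heritability statement under the primary objective rests on this assumption. A report that followed the plan could say that the assumption had been tested, and give a result either way, when the data had not addressed it.

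**Working it through.** The article gives no operating figure for this model, so there is none to reproduce.

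**Inputs.** 31 MZ and 14 DZ pairs (Table 1); 5% significance level (section 3); the 2:1 additive pattern (Introduction); earlier FMD-response correlations 0.74/0.37 and planning values 0.80/0.30 (section 3.2). Assumed: zero DZ covariance not rejected at 5%, two-sided, counts as a flag.

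**Step 1: identification.** Let shared environment be Cmz in MZ and Cdz in DZ pairs. Then

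rMZ = A + Cmz, rDZ = A/2 + Cdz,

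and the assumption is Cmz = Cdz. Two correlations cannot fix three unknowns:

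- A = 0.80, Cmz = Cdz = 0 (assumption true): rMZ = 0.80, rDZ = 0.40.
- A = 0.40, Cmz = 0.40, Cdz = 0.20 (violated): rMZ = 0.40 + 0.40 = 0.80, rDZ = 0.20 + 0.20 = 0.40.

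The usual estimate 2(rMZ - rDZ) equals A + 2(Cmz - Cdz). It is 0.80 in both cases, which doubles the true A in the second. No comparison based on rMZ and rDZ alone can tell them apart. With non-negative components, rDZ = 0 needs A = 0 and Cdz = 0, one extreme corner of the possible violations.

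**Step 2: analytic chance of not rejecting rDZ = 0 with 14 pairs.** The standard error of Fisher's z for an intraclass correlation is 1/√(14 - 1.5) = 1/√12.5. With m = atanh(rDZ) × √12.5,

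P(not rejected) = Φ(1.96 - m) - Φ(-1.96 - m).

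| rDZ | m | P(not rejected) |
|---|---|---|
| 0.20 | 0.72 | 89% |
| 0.30 | 1.09 | 81% |
| 0.37 | 1.37 | 72% |
| 0.40 | 1.50 | 68% |
| 0.50 | 1.94 | 51% |

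rMZ does not enter the formula.

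**Step 3: simulation.** 31 MZ and 14 DZ pairs, likelihood ratio of the free model against DZ covariance = 0. Scenarios with the same correlations have the same flag rate by construction.

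| rMZ/rDZ | Components | Assumption holds? | Flagged |
|---|---|---|---|
| 0.60/0.30 | A 0.60 | yes | 78% |
| 0.74/0.37 | A 0.74 | yes | 71% |
| 0.80/0.40 | A 0.80 | yes | 66% |
| 0.80/0.40 | A 0.40, Cmz 0.40, Cdz 0.20 | no | 66% |
| 0.80/0.50 | A 0.60, C 0.20 | yes | 49% |
| 0.80/0.50 | A 0.30, Cmz 0.50, Cdz 0.35 | no | 49% |
| 0.80/0.30 | A 0.60, Cmz 0.20, Cdz 0 | no | 80% |
| 0.80/0.20 | A 0.40, Cmz 0.40, Cdz 0 | no | 90% |

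Repeat runs agree within a few points (79%, 69% and 68% for the first three rows).

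**Step 4: other decision rules.** If a significant rMZ v rDZ test is also required, as it is before A is calculated, the sound traits at 0.60/0.30, 0.74/0.37 and 0.80/0.40 are flagged in 27%, 48% and 57%. Across repeat runs the range is about 22-58%. If instead the zero-DZ model is preferred on AIC over the free model, they are flagged in 59%, 47% and 46%.

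**The case against.** Four points can be made for the plan.

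- The wording is cautious: the model is to show whether the correlations suggest a violation. An rDZ near zero with a clearly positive rMZ does contradict the additive pattern, so the model can pick up one extreme symptom. This stands, but dominance, epistasis or sampling error in 14 pairs produce the same symptom.
- The decision rule behind every percentage above is inferred. This stands, and a fuller plan may state one. The rates move with the rule; the identification argument in Step 1 needs no rule at all.
- No variance component depends on this model, and rMZ and rDZ are reported with confidence intervals regardless. This stands. The text does not say that a flagged outcome is discarded or an unflagged one validated, so the fault lies in interpretation and not in the estimates.
- The obvious replacement, rMZ - 2rDZ, does not test the assumption either. This also stands, and the fix says so.

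A reader might also infer that the check works backwards, flagging sound traits more often than violated ones. The documents do not support that as a general statement. It is true where the violated trait has the higher rDZ (49% at 0.80/0.50 against 66% for the sound trait at 0.80/0.40). It reverses where DZ twins share little or no environment (80% and 90% at 0.80/0.30 and 0.80/0.20). At equal correlations the rates are the same.

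**Conclusion.** The plan is wrong as written: the zero-DZ model does not test the equal environments assumption, and rMZ and rDZ alone cannot test it. That follows from the Introduction's own account of the twin design and rests on no simulation.

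The size rests on assumptions: normal data, all 31 and 14 pairs analysed, and non-rejection at 5% read as a violation. Under these, about 66-78% of sound additive traits with rMZ 0.60-0.80 would be flagged, or about 22-58% if the two correlations must also differ significantly. Fewer DZ pairs after the adherence rule would raise the first range. The outcome is driven by rDZ and the number of DZ pairs.

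This should be corrected because it concerns the assumption behind the primary objective for every outcome. It does not invalidate the A, C and E estimates.

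**What to change.** - Stop describing the zero-DZ model as a test of the equal environments assumption, and state the assumption as untested by these data.
- Report rMZ - 2rDZ with a confidence interval for each outcome as a check on the fit of the additive ACE model. A positive value points to non-additive effects or a negative C. The check is relevant here because the planning values give 0.80 - 2(0.30) = 0.20, that is C = 2(0.30) - 0.80 = -0.20, outside that model.
- Say plainly that this check is imprecise and does not test the assumption. At 0.80/0.40, taking SE(r) ≈ (1 - r²)/√(n - 1.5), SE(rMZ) = 0.36/√29.5 = 0.066 and 2 × SE(rDZ) = 2 × 0.84/√12.5 = 0.475. The combined SE is √(0.066² + 0.475²) = 0.48, so the 95% interval is about ±0.94.
- Optionally, use section 2.7.1, where "when they were DNA zygosity tested 10 self-reported DZ twin pairs were actually found to be MZ". Tabulate within-pair correlations for these pairs against the other MZ pairs, descriptively only. First confirm how many of the 10 are among the 31 enrolled MZ pairs, which the article does not say, and which of them chose to receive their DNA result, since after that they would no longer have believed they were DZ.

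The cost is two sentences and one column in the results tables, with no new data. The optional table costs a little more, and even if all 10 pairs qualify it compares only 10 with 21.
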